# Virtual restorative environment therapy as an adjunct to pain control during burn dressing changes: study protocol for a randomised controlled trial

**DOI:** 10.1186/s13063-015-0878-8

**Published:** 2015-08-05

**Keywords:** procedure-related pain, distraction, virtual reality, burns, pilot study, randomised controlled trial

## Abstract

**Background:**

The pain of a severe burn injury is often characterised by intense background pain, coupled with severe exacerbations associated with essential procedures such as dressing changes. The experience of pain is affected by patients’ psychological state and can be enhanced by the anxiety, fear and distress caused by environmental and visual inputs. Virtual Reality (VR) distraction has been used with success in areas such as burns, paediatrics and oncology. The underlying principle of VR is that attention is diverted from the painful stimulus by the use of engaging, dynamic 3D visual content and associated auditory stimuli. Functional magnetic resonance imaging (fMRI) studies undertaken during VR distraction from experimental pain have demonstrated enhancement of the descending cortical pain-control system.

**Methods/Design:**

The present study will evaluate the feasibility of introducing a novel VR system to the Burns Unit at the Queen Elizabeth Hospital Birmingham for dressing changes: virtual restorative environment therapy (VRET). The study will also explore the system’s impact on pain during and after the dressing changes compared to conventional analgesia for ward-based burn dressing changes. A within-subject crossover design will be used to compare the following three conditions:Interactive VRET plus conventional analgesics.Passive VRET with conventional analgesics.Conventional analgesics alone.

Using the Monte Carlo method, and on the basis of previous local audit data, a sample size of 25 will detect a clinically significant 33 % reduction in worst pain scores experienced during dressing changes.

**Discussion:**

The study accrual rate is currently slower than predicted by previous audits of admission data. A review of the screening log has found that recruitment has been limited by the nature of burn care, the ability of burn inpatients to provide informed consent and the ability of patients to use the VR equipment. Prior to the introduction of novel interactive technologies for patient use, the characteristics and capabilities of the target population needs to be evaluated, to ensure that the interface devices and simulations are usable.

**Trial registration:**

Current Controlled Trials ISRCTN23330756. Date of Registration 25 February 2014.

## Background

The management of severe burns involves meticulous wound care in order to prevent infection. This necessitates regular debridement and dressing changes over a period of days to weeks. This form of wound care is recognised as one of the most painful procedures that can be undertaken, with some patients reporting severe to excruciating pain [1]. Poor acute pain management can have long-lasting consequences and is associated with adverse physical and psychological sequelae such as persistent pain, depression, post-traumatic stress disorder and, at the extreme, suicidal ideation [2–4]. Initial dressing changes and wound care requiring skin grafting are usually carried out under general anaesthesia. Subsequent wound care may be undertaken on a regular basis, often daily, with the benefits of general anaesthesia exceeded by the risks of anaesthesia and the practical constraints of operating theatre access. Currently, sedoanalgesia or opioid-based analgesia, in addition to other agents such as paracetamol, is used for pain relief during ward-based wound care [5], but these agents have multiple unpleasant side effects. Some units use distraction techniques informally or as part of a multi-modal approach to pain relief. These range from simple interventions such as video watching or listening to music, to more high tech interventions such as virtual reality (VR)-based computer systems [3].

Computer-generated, three-dimensional ‘virtual’ worlds have existed in the fields of gaming, education and simulation for nearly three decades [6] with applications in the medical domain only reaching an acceptable level of maturity in the past 5 to 10 years or so [7, 8]. Computer hardware, such as motion-tracking, head mounted displays and noise-cancelling headphones, allows ‘immersion’ in, and interaction with, a virtual environment. Pain is enhanced by the anxiety, fear and distress caused by environmental and visual inputs. The underlying principle of VR is that attention is diverted from the painful stimulus through the use of engaging, dynamic content presented (primarily) visually and aurally, with some systems capable of delivering force and touch (haptic) sensations and limited olfactory stimulation. Functional magnetic resonance imaging (fMRI) studies undertaken during VR distraction from experimental pain have demonstrated enhancement of the descending cortical pain-control system via activation of the perigenual anterior cingulate cortex and periaqueductal grey matter [9]. A number of studies have investigated the use of VR during painful burn management and physiotherapy, showing a statistically and clinically significant reduction in pain scores of around 30 % [10–12]. It has been found to be especially effective for those experiencing severe pain [10]. Preliminary studies also suggest that the effectiveness of VR does not decline with multiple treatments, with studies showing it retained its analgesic potency over multiple sessions [13, 14].

Viewing natural environments has been shown to have therapeutic benefits, including improved pain relief and post-operative recovery [15]. Indeed, static images have recently been introduced to the Burns Unit at the Queen Elizabeth Hospital, Birmingham (QEHB). Many of these, however, are not visible to patients within their rooms. A view of nature could be provided as a virtual world - bringing the restorative natural environment to the patient’s bedside. No system to date has integrated a virtual restorative environment with distraction therapy [16–18].

Acceptance of interactive technologies, including virtual reality, by the users (patients and staff) is dependent on usability (in some cases, wearability), utility and affordability. Developments driven by the gaming industry have resulted in rapid advancements in affordability, portability and ubiquity of computer systems [19, 20]. These advances present great opportunities to develop and evaluate a novel VR system for pain management at the patient bedside, using commercially available off-the-shelf equipment. Low-cost devices have been developed by other users, but use commercial video games, designed for use by children [21].

Using an active human-centred approach to prototype development and considering context, ergonomics and task completion increases the usability and utility of the intervention [22].

Efficacy of our proposed system is based on previous work on VR distraction [23, 24]. Uniquely, our proposed system will integrate distraction therapy with the development of virtual restorative environments that are designed to appeal to adults. We have termed our system ‘Virtual Restorative Environment Therapy’ (VRET).

### Context

The environmental context of burn patients and their carers at QEHB is a teaching hospital with a specialist burns unit. Most patients are in generously proportioned single or double rooms, but most lack windows with a view and natural light. The prototype system must be mobile and easily moved between patient bed spaces, with appropriate decontamination procedures to minimize the risk of cross-infection.

### Ergonomics

The pattern of burn injury will vary between every patient. As patients may have restrictions to movement and hand or arm function, interface devices, such as commercial, off-the-shelf (COTS) hand controllers and gamepads, can be chosen or modified to allow optimum use by those with the greatest functional deficits. Some analgesics, for example opiates and antidepressants, may affect perception and coordination [25]. These factors have been considered in the development of the VR system, particularly with regard to the fidelity of the images presented and the mapping of the functions of the control devices used onto the computer-generated objects displayed on screen [26].

### Task

A priority of the prototype design is to ensure that the process of changing the dressing is in no way hindered. The layout of the patient, bed, equipment trolley and nursing staff will vary depending on the location of the burn wounds. The VRET prototype has been configured to allow flexibility in screen location and patient access. Free-flowing water is also used for some dressing changes to enhance tissue and dressing removal. Full immersion in water, or the use of a ‘hydrotank’ is not used during dressing changes at QEHB, removing the requirement for a fully waterproof system [27].

### Hypothesis

When compared to standard analgesia alone, adjunctive immersive interaction with a virtual environment will reduce pain during ward-based burn dressing changes.

### Aims

To assess the efficacy of the immersive virtual reality system in terms of the following:The effects on the pain experienced by patients during painful procedures requiring multimodal analgesia but not requiring sedation/anaesthesia.The effects on the anxiety experienced by patients during painful procedures not requiring sedation/anaesthesia.The system’s ability to generate a sense of presence on the part of the VR users^1^User acceptance experienced by the patients and usability feedback.User acceptance by the clinical staff caring for the patients.

## Methods/Design

This study will be a single-centre block-randomised cross-over trial.

### Ethics

This study has been approved by the National Research Ethics Service Committee South Birmingham (Reference 13/WM/0205) and registered with the UK Clinical Research Network portfolio (Study ID 15785) and Current Controlled Trials (ISRCTN23330756).

**Fig. 1 Fig1:**
[figure not shown]
Virtual restorative environment therapy (VRET) system *in situ*, viewed from the rear

**Fig. 2 Fig2:**
[figure not shown]
Screenshot of the speed boat game viewed on laptop

### Study participants

#### Inclusion criteria

Inclusion criteria are patients with burns (any cause) admitted to the Queen Elizabeth Hospital Burns Unit requiring the following:at least three in-patient dressing changes.opioid-based analgesia (for example, oral morphine, codeine phosphate or tramadol) or inhaled nitrous oxide (entonox) for the dressing change (that is, patients who may potentially experience moderate or severe pain).

#### Exclusion criteria

Exclusion criteria include the following:Inability to use the VRET equipment (for example, blindness or severe bilateral hand injuries).Requirement for general anaesthesia or sedation with ketamine or midazolam.Poor cognitive state (for example, severe dementia, delirium or severe psychiatric illness).Multidrug-resistant infection (due to potential equipment contamination, although low risk, this criterion is appropriate for the feasibility study).Dressing changes requiring overhead showering

### Randomisation process

The order of intervention will be randomised using block allocation, as is appropriate for the small sample size [31]. A computer-generated randomisation sequence will use a block size of six, which will be repeated four times.

### Sample size

Using a Monte Carlo method, we estimate that a sample size of 25 patients would provide 99 % power to detect a clinically important effect. The data and assumptions underlying the calculation are as follows:The observed distribution of 33 pain scores in a recent audit is the true distribution of the ‘control’ value.The mean percentage reduction from the control value is 30 for interactive VRET. This value has been chosen as it has been demonstrated that the patient-determined, clinically important improvement reduction in pain experienced corresponds to 33 % reduction in measured pain, using an 11-point numerical rating scale [32].The mean percentage reduction from the control value is 15 for passive VRET.Both percentage reductions are normally distributed with a standard deviation of 25.The nonparametric Friedman test (with a significance level of 5 %) will be used to compare the pain scores under the three conditions.

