### Data analysis

Data will be analysed using IBM SPSS 20.0. Normality will be assessed using the Shapiro-Wilk Test. When comparing the three conditions the repeated measures analysis of variance (ANOVA), assuming normality, or the Friedman test will be used. When comparing passive or active VRET conditions to the control condition, the Wilcoxon signed rank test will be a possible alternative to a paired *t* test.

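### The 5 % level and 99 % power belong to a three-condition Friedman test, while the only hypothesis is active VRET versus standard analgesia; the deciding contrast should be named

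*Protocol article*

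**What the plan says.** The protocol article (Background, Hypothesis) gives one hypothesis: "When compared to standard analgesia alone, adjunctive immersive interaction with a virtual environment will reduce pain during ward-based burn dressing changes". This compares one VRET condition with control and has a direction.

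Sample size states that "we estimate that a sample size of 25 patients would provide 99 % power to detect a clinically important effect". The assumptions beneath it include "The mean percentage reduction from the control value is 30 for interactive VRET", "The mean percentage reduction from the control value is 15 for passive VRET", a standard deviation of 25 for both reductions, and control scores distributed as in an audit of 33 scores that are not shown. The last item is a Friedman test at the 5 % level, which "will be used to compare the pain scores under the three conditions". No other significance level or power appears in the article.

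Data analysis names repeated measures ANOVA or Friedman for the three conditions. It then adds: "When comparing passive or active VRET conditions to the control condition, the Wilcoxon signed rank test will be a possible alternative". The method it would replace is the paired t test. The section gives no order, no condition linking the pairwise tests to the three-condition test, and no statement of which result decides the hypothesis. Outcome measures names worst pain on the 11-point scale as primary. That fixes the variable but not the contrast.

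**The concern.** The hypothesis and the sized test ask different questions. Friedman asks whether the three conditions share one distribution of ranks. Rejection means that at least one condition differs. It does not say which one or in which direction, so it cannot by itself confirm that active VRET lowers pain relative to control.

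This matters because passive VRET is expected to work too: the plan assumes a 15 % reduction for it. A significant omnibus result could therefore come from either VRET condition. With no deciding contrast named, the authors could choose after seeing the data whether the three-condition test, the active comparison or the passive comparison carries the conclusion. The 99 % would also stand beside a hypothesis for which it was not calculated.

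**Working it through.** **Inputs.** From Sample size: n = 25; reductions distributed N(30, 25) for active and N(15, 25) for passive VRET, in per cent of the control score; Friedman at 5 %. The audit scores are not given, so control scores are an assumption. Six shapes on 0-10 were tried: uniform 0-10, 1-10 and 4-10; rounded normal with mean 6 and SD 2.5; rounded normal with mean 4 and SD 3; and a strongly low-skewed shape. The correlation between the two reductions is also not stated, so 0 and 0.5 were used.

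**Model.** Active = control × (1 − reduction/100), and likewise for passive. Scores were either left as they fell or rounded and clipped to 0-10.

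**Step 1: the plan's own figure.** Friedman power at n = 25 came out at 0.97-1.00 over all shapes, and 0.985-0.999 without the strongly low-skewed one. The stated 99 % reproduces, and it is omnibus power.

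**Step 2: what that test can respond to.** Same model, with mean effect zero for active VRET and independent reductions:

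| True effect | Friedman significant at 5 % |
|---|---|
| passive 30 %, active 0 | about 98-99.9 % for most control shapes; about 96 % at the lowest, for the strongly low-skewed shape |
| passive 15 %, active 0 | about 50-69 % for most shapes; about 45 % at the lowest, for the strongly low-skewed shape |

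The hypothesis is false in both rows.

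**Step 3: power by contrast.** Wilcoxon signed rank, two-sided 5 %, n = 25, plan's effects (30 and 15):

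| Contrast | Power over assumed shapes |
|---|---|
| active v control | 0.98-1.00 (0.96-1.00 at 2.5 %) |
| passive v control | 0.55-0.90; up to 0.94 with other assumed shapes |

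A rough check that needs no control distribution treats the percentage reductions themselves as the data. Power ≈ Φ(mean/SD × √n − 1.96).
- Active: 30/25 × 5 − 1.96 = 4.04, so power is above 99.9 %.
- Passive: 15/25 × 5 − 1.96 = 1.04, so power is about 85 %.

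**Step 4: error rate (supporting only).** If both pairwise tests were run at 5 % with no gate or adjustment, independence would give 1 − 0.95² = 9.75 %. Allowing for the shared control, simulation under the global null gives about 8.8 %. Running them only after a significant Friedman test gives about 3.4 % under the global null. Bonferroni gives about 4.5 %.

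**The case against.** The strongest reply is that the hypothesis does have a test. Data analysis lists active versus control, and nothing in the article calls Friedman the primary test or says that its significance establishes the hypothesis. When only passive VRET works, the listed active comparison correctly shows no benefit in roughly 90-98 % of simulated trials. Requiring both a significant Friedman test and a significant active comparison still leaves roughly 97-100 % power under the plan's effects. All this stands, and it limits the point to naming the deciding contrast.

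The study also describes itself partly as a feasibility study, which argues against strict confirmatory demands. That carries some weight, but the article states efficacy aims, a hypothesis and a formal power figure, and these should agree with one another.

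Four stronger readings are tempting and are not supported:
- **The trial is too small.** Active versus control has about 98-100 % power at 25 patients under the plan's assumptions.
- **The pairwise tests have an uncontrolled error of 9 % or more.** That holds only if no gate or adjustment exists. The article is silent, and a full protocol or analysis plan that is not shown may supply one. Its order, three conditions first and then comparisons with control, is also compatible with a gate.
- **The 99 % is claimed for every comparison.** Sample size lists the Friedman test among the assumptions of the calculation. The abstract's statement that 25 patients will detect a 33 % reduction does read like a pairwise claim, but it makes no such claim for the passive condition.
- **Active versus passive is underpowered.** Data analysis does not plan that comparison.

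**Conclusion.** The mismatch is real and visible in the article's own text: a directional contrast of one condition with control as hypothesis, and a non-directional three-condition test as the only one with a level and a power. Under the plan's model the sized test would almost always be significant when passive VRET alone produced a 30 % reduction, so it cannot by itself decide the hypothesis. The consequence is ambiguity about which result counts. It is neither a shortage of patients nor an untested hypothesis.

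The simulated figures rest on assumed control scores and, for the percentage reductions, on the plan's own normal model. The conclusion on active versus control is stable over the shapes tried. The figure for passive versus control is not, and only the authors can settle it from their audit data. The family-wise figure of about 9 % is conditional on no gate or adjustment existing and does not carry the finding. Severity: should fix.

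**What to change.** In Data analysis, name the within-patient comparison of active VRET with control in worst pain as the single primary test at two-sided 5 %. Test passive versus control at 5 % only if the primary test is significant; this fixed order holds the family-wise error of the two comparisons at 5 %. Make the three-condition test secondary.

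In Sample size, state that the 99 % is the power of the Friedman test. Add the power for active versus control and for passive versus control, both recomputed by the authors from their audit distribution. The ranges given here show what to expect and are not values to print.

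The cost is wording in two sections and a rerun of the existing simulation. No extra patients are needed. The stated power for the passive comparison becomes less favourable, and passive VRET cannot be claimed as effective if the active comparison fails. Trial status reports eight patients enrolled with enrolment ongoing at submission; any such change should be dated and made before the data are compared by condition.

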### Procedure

Patients will be informed of the study by their clinical team. Patients meeting the inclusion criteria will be invited to participate by the research team, following which they will have 12 to 24 h to decide whether they wish to enrol in the study, at which point written informed consent will be taken.

Each patient will receive each condition; active VRET, passive VRET and control. The order will be randomised prior to the first procedure.

Analgesia will be provided as per ward protocol for each intervention and patient requirement prior to dressing change. Dressing changes will be carried out as usual by ward staff. Regular analgesics will be given at set times according to prescription (for example, 07:00, 12:00, 14:00, 17:00, 22:00) and, as required, analgesia will be given 30 to 60 min prior to a dressing change. These timings will be recorded. Breakthrough pain is managed by nurse-titrated boluses of intravenous morphine.

For conditions utilising the VRET equipment, a member of the research team will set up the equipment in the patient room/bed space and patients will receive a 5 to 10 min tutorial/demonstration prior to their dressing change. The setup procedures for the VRET system will be demonstrated to the nurse undertaking the dressing change to allow evaluation of nursing perception of the system, including ease of use.

A member of the research team will remain in the room whilst the dressing change is undertaken by a member of the burn unit’s nursing team in order to detect adverse events or troubleshoot where required. Their intervention will be the minimum possible in order to allow normal clinical proceedings. Following the dressing change, a member of the research team will remove the equipment from the patient’s bed space/room, decontaminate it and store it safely.

A researcher, who has been blinded to the intervention, will return one hour following the dressing change, to collect the questionnaire data from the patient on their experience of pain, anxiety and nausea during their dressing change. Despite the disadvantage of relying on recalled pain by the patient, asking patients questions during the distraction activity could impact the efficacy of the analgesic intervention. Likewise, asking questions during the control condition could be distracting in itself. This methodology will be repeated for the two subsequent dressing changes. At the end of the study period, patients will be offered the use of the VRET system for future dressing changes if they found it beneficial.

The member of the research team present for the dressing change will then undertake a semi-structured interview and questionnaire of the patient and nursing staff to assess their user acceptance of the prototype VRET system.

